#### Exclusion criteria

2.4.3

Participants who meet ≥1 of the following criteria will not be considered eligible to participate in the clinical study. The exclusion criteria are:

1.Having medical or surgical diseases unsuitable to participate in this study, as assessed by health professionals.2.Pregnancy or breastfeeding (for female participants).3.Having other competitive conditions that can cause peripheral neuropathy.4.Participants involved in the planning or execution of this study.5.Having severe cognitive impairment and difficulty to understand the clinical trial protocol.6.Unable to receive moxibustion treatment due to any reasons.

### Discontinuation criteria

2.5

Participants are encouraged to complete all study evaluations, they may withdraw from the clinical study at any time and for any reason. Every effort will be made to determine why any participants withdraw from the study prematurely. This information should be recorded. If a participant prematurely, all data normally collected at discharge should be collected at the time of premature discontinuation or the scheduled discharge. Participants may be terminated before completing the clinical study for any of the following discontinuation criteria are:

1.Participants have serious adverse reactions during the clinical trials and it is not suitable to continue participating in this study.2.Participants have serious clinical complications or deteriorating medical conditions during the clinical trials.3.Participants ask to terminate the trial halfway.4.Participants show poor compliance and cannot comply with the clinical trial protocol.

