### Study procedure

2.7

At visit 1, the study clinical researcher will check the participants’ vital signs, medical history, physical examination, algometry pain assessment, the Leeds assessment of neuropathic symptoms and signs (LANSS) pain scale, VAS, the Neuropathy Pain Scale (NPS), functional performance capacity with 6 minutes walking test, the foot and ankle ability measure (FAAM), and laboratory tests (includes, serum HbA1c, and serum albumin levels). The intervention group will received moxibustion management for 30 minutes. In the meantime, the clinical researcher will check the participants’ adverse effects.

From visit 2 to 24 (8 weeks), the intervention group will be treated the same manner as visit 1, and clinical researcher will be check the participants’ algometry pain assessment, the LANSS pain scale, VAS, the NPS, functional performance capacity with 6 minutes walking test, the FAAM, and laboratory tests (includes, serum HbA1c, and serum albumin levels) on visit 12 and visit 24.

At visit 25 (follow-up), the clinical researcher will check the participants’ adverse effects and measured the same manner as visit 12 and visit 24.

If any additional visits may be performed at any time by the clinical researcher's judgment, or following the participant's request. In the event of an unexpected visit, the following tests and assessment will be performed: vital signs, checking adverse events, and laboratory tests. The detailed study period is shown in Table 1.

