#### Control group

2.8.2

No intervention will be conducted on the control group.

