#### Primary outcome measure

2.9.1

Pain assessment measured with Algometry: It is used to determine sensitivity to pain produced by pressure.

Pain assessment measured with the LANSS: The LANSS Pain Scale is based on analysis of sensory description and bedside examination of sensory dysfunction, and provides immediate information in clinical settings.^[12]^ The possible scores range from 0 to 24, with a score of ≥12 considered to be suggestive of neuropathic pain.

Pain assessment measured with the VAS: A VAS is a measurement instrument that tries to measure a characteristic or attitude that is believed to range across a continuum of values and cannot easily be directly measured. It is often used in epidemiologic and clinical research to measure the intensity or frequency of various symptoms.

Pain assessment measured with the NPS: Scores are based on patient responses to questions about pain intensity. 0 indicates no pain; 10 indicates the most pain imaginable. The NPS is only for use in patients who have already been diagnosed with neuropathic pain.^[13]^

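### Section 2.5 lets health problems or poor compliance end study participation, not only moxibustion, and one data set at exit satisfies it, so later scheduled outcomes may go uncollected

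*Protocol article*

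**What the plan says.** Section 2.5 (Discontinuation criteria) opens on a helpful note: "Participants are encouraged to complete all study evaluations". It then states the power to end participation: "Participants may be terminated before completing the clinical study for any of the following discontinuation criteria". Four criteria follow.

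- Criterion 1 is a serious adverse reaction, where continuing in the study is judged unsuitable.
- Criterion 2 reads "Participants have serious clinical complications or deteriorating medical conditions during the clinical trials" and carries no such qualifier.
- Criterion 3 is the participant's own request.
- Criterion 4 is poor compliance with the protocol.

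For those who leave early, the data rule is that "all data normally collected at discharge should be collected at the time of premature discontinuation or the scheduled discharge".

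Section 2.7 (Study procedure) schedules the pain, function and laboratory outcomes at visit 1 and again at visits 12, 24 and 25. It also allows extra visits with a fixed content: "In the event of an unexpected visit, the following tests and assessment will be performed: vital signs, checking adverse events, and laboratory tests". Section 2.8.2 says of the waiting group: "No intervention will be conducted on the control group".

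**The concern.** Stopping a treatment and stopping observation are separate decisions, and section 2.5 treats them as one. A patient with a burn or a worsening foot may well need to stop moxibustion. It does not follow that the remaining pain and function scores should stop too. In the waiting group there is no trial treatment to stop, so termination under criterion 2 ends observation and nothing else.

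The reasons for removal are not neutral. Deterioration of a diabetic patient can plausibly affect neuropathic pain, walking distance, HbA1c and albumin, which are the trial's outcomes. Poor compliance can plausibly depend on the treatment, because the moxibustion group must attend three sessions a week and the waiting group has none. Outcomes lost under criteria 1, 2 and 4 may therefore be missing for reasons connected with what is being measured. An analysis plan can choose how to handle missing values but cannot restore visits that never took place.

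**Working it through.** **Text check.** The plan gives no figure on this point, so the first step is to compare the rules.

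1. What ends: participation in the study (section 2.5). The text does not distinguish this from ending moxibustion.
2. What must be collected: the discharge data, at exit *or* at the scheduled discharge (section 2.5). Because these are alternatives, a set taken at exit complies. The article does not itemise that set. I take it to be the full outcome battery, which is the reading most favourable to the plan.
3. What else could supply the later outcomes: the opening encouragement in 2.5 is not a requirement, and the listed content of extra visits in 2.7 has no pain or function measure.
4. Scheduled assessments left unsecured when data are taken only at exit: 3 if exit is before visit 12, 2 if between visits 12 and 24, and 1 if between visits 24 and 25.

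**Possible size.** Inputs from the document: 40 patients at 1:1 (section 2.2), so 20 per arm. Assumed inputs: k = 1 or 2 patients removed, in one arm only, with normally distributed scores in SD units.

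*Yardstick.* SE of the difference = sqrt(2/20) = 0.316 SD.

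*(a) The exit set stands in for visit 24.* If the score would have moved by d (assumed 0 to 1 SD) between exit and visit 24, the arm mean is off by (k/20) × d.
- k = 1: 0 to 1/20 × 1 = 0.05 SD, up to 0.05/0.316 = 0.16 SE.
- k = 2: 0 to 2/20 × 1 = 0.10 SD, up to 0.10/0.316 = 0.32 SE.

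*(b) The exit set is not used because it falls at another time point.* The expected largest and second-largest values of 20 standard normal scores are 1.867 and 1.408. If exactly the worst scorers are removed, the expected shift is their sum divided by (20 − k).

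| Link between removal and score | k = 1 | k = 2 |
|---|---|---|
| None | 0 | 0 |
| Correlation 0.5 (simulated) | 0.049 SD | 0.091 SD |
| Exactly the worst removed | 1.867/19 = 0.098 SD | (1.867 + 1.408)/18 = 0.182 SD |
| The last row in SE | 0.098/0.316 = 0.31 | 0.182/0.316 = 0.58 |

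The entries in (b) are averages over samples. In simulation, with the two worst scorers removed, the shift exceeded 0.6 SE in about 40% of samples. Equal removal of the same kind in both arms cancels on average.

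**The case against.** The strongest reply is that this is a condensed article and that follow-up of terminated patients belongs in the full protocol. Section 2.5 is also milder than the concern suggests. It is permissive, it encourages completion of all evaluations, it allows collection at the scheduled discharge, and it does not forbid continued assessment. The problem arises only if staff terminate a patient and then measure only at exit. This reply lowers the grade but does not remove the point: the article states a rule, and that rule can be followed exactly while the later outcomes are lost.

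A second reply concerns safety. Participation includes algometry, a walk test and blood sampling even in the waiting group, and ending these can be right for a seriously ill patient. That stands. A reader might infer that terminating a waiting-group patient is never justified; the article does not support that. The remedy therefore needs a clinical exception.

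A third reply is that telephone follow-up recovers little. This is largely correct. The NPS is suited to it, since "Scores are based on patient responses to questions about pain intensity", and so is the self-reported FAAM. The LANSS is not, because it rests on "analysis of sensory description and bedside examination of sensory dysfunction". Algometry, the walk test and blood tests are also lost, and telephone scores may differ from those taken in person.

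Adverse event duration and resolution are already required by section 2.10 and are not part of this point.

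**Conclusion.** The point holds as a weakness in a stated rule. Section 2.5 lets criteria 1, 2 and 4 end participation, one exit data set satisfies its data rule, and the outcomes at visits 12, 24 and 25 may then go uncollected for reasons related to health or treatment.

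Three stronger conclusions are tempting and are not supported.

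- That the trial will be biased in favour of moxibustion: the criteria apply to both arms and no removal rate is given, so neither direction nor size can be determined.
- That these outcomes will be lost: the wording permits the loss but does not impose it.
- That 0.58 standard errors is a ceiling: it is an expected value under an assumed extreme pattern, and single samples can exceed it.

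Under the assumed 1 or 2 removals of 20 in one arm, the expected shift runs from about 0 up to 0.10 or 0.18 SD. In a 40-patient pilot that is probably modest. Grade: COULD.

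**What to change.** Amend section 2.5 so that:

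- criteria 1, 2 and 4 stop moxibustion where needed and do not by themselves end follow-up;
- unless consent is withdrawn or assessment is clinically unsuitable, the discharge data are collected at exit *and* the patient, in either arm, stays on the remaining scheduled visits 12, 24 and 25. This replaces the present choice between exit and scheduled discharge;
- as an optional fallback, the masked assessor takes the self-reported scores by telephone (NPS and FAAM, and VAS only if it can be taken remotely), flagged as a different mode. Algometry, the LANSS examination, the walk test and blood tests are then accepted as missing.

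Cost: a wording change and at most 3 contacts per removed patient. For an assumed 1 to 4 such patients among 40, that is 1 × 3 = 3 to 4 × 3 = 12 contacts, each a call or an already scheduled visit. The downsides are some staff time, some burden on unwell patients, and a possible mode difference in telephone scores. The right to withdraw is unchanged.

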#### Intervention group

2.8.1

After randomization, patients of intervention group will receive moxibustion treatment provided by registered physician at TCM Skill Training Centre, Xiamen University Malaysia. The clinical researchers will perform indirect moxibustion on Hegu (LI4), Fenglong (ST40), Quchi (LI11), Sanyinjiao (SP6), Zusanli (ST36), and Taichong (LR3). The treatment session will take 30 minutes per session, and will be done for 3 times per week, lasting for 8 weeks. All moxibustion management was performed by an experienced TCM practitioners in the School of Traditional Chinese Medicine, Xiamen University Malaysia, and also registered practitioners in the Division of Traditional & Complementary Medicine, Ministry of Health Malaysia.

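### Section 2.5 allows poor compliance to end study participation and leaves the timing of the final measurement open, which permits outcome loss mainly from the moxibustion arm

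*Protocol article*

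**What the plan says.** Section 2.5 (Discontinuation criteria) opens by encouraging participants to complete all evaluations. It then states "Participants may be terminated before completing the clinical study for any of the following discontinuation criteria", and the fourth criterion is "Participants show poor compliance and cannot comply with the clinical trial protocol". It sets no threshold for poor compliance, names no arm and does not say who decides. For a participant who stops early, "all data normally collected at discharge should be collected at the time of premature discontinuation or the scheduled discharge".

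Section 2.8.1 (Intervention group) says the moxibustion sessions "will be done for 3 times per week, lasting for 8 weeks". Section 2.8.2 (Control group) says "No intervention will be conducted on the control group".

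Section 2.7 (Study procedure) places the outcome assessments after baseline "on visit 12 and visit 24", and at visit 25, where participants are "measured the same manner as visit 12 and visit 24". These assessments are written for participants in general, not for one arm.

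Section 3 (Data analysis) names no analysis population and does not say that terminated participants are excluded.

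**The concern.** Criterion 4 ends study participation, not only treatment. It is a conduct rule, so it decides which outcome data will exist. No analysis plan, seen or unseen, can recover a week 8 measurement that was never taken.

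The two arms carry very different compliance burdens, so a compliance rule that names no arm will probably not act equally on both. If patients who miss sessions tend to be those who feel no benefit or tolerate the treatment badly, ending their follow-up leaves a selected moxibustion arm beside a nearly complete waiting arm. The open timing adds a second problem: a value taken at exit in, say, week 3 is not comparable with a week 8 value in the other arm, yet both satisfy the text.

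**Working it through.** **Burden in each arm.**
- Moxibustion: 3 sessions per week × 8 weeks = 24 sessions (section 2.8.1).
- Waiting group: 0 sessions (section 2.8.2).
- Both arms: three post-baseline assessments, at visits 12, 24 and 25 (section 2.7). At three visits per week, visit 12 is week 12/3 = 4 and visit 24 is week 24/3 = 8. With the 4-week follow-up period, visit 25 is taken as week 8 + 4 = 12.

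A waiting-group participant can fail to comply only by missing assessments. A moxibustion participant can also miss any of 24 sessions. Losses mainly from moxibustion are therefore likely, but not losses from that arm alone.

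**Timing of the final measurement.** Section 2.7 fixes assessments at numbered visits. Section 2.5 allows discharge data that "should be collected at the time of premature discontinuation or the scheduled discharge". Its second option keeps the planned time and its first does not. Nothing says which applies, and section 2.7 does not label a visit as discharge.

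**Possible size.** The protocol gives no effect size, SD, power, dropout rate or compliance rate, so there is no figure to reproduce. What follows is an illustration.
- From the document: 40 participants at 1:1, hence 20 per arm; P < .05, taken as two-sided, so 2.5% in each direction.
- Assumed: no true effect; unit SD; unpaired t test; a latent compliance score with correlation ρ to a good outcome; the k least compliant of 20 removed and left out of the analysis.

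Expected bias = ρ × (m for moxibustion − m for control), where m is the mean compliance score of those who remain. For 20 standard normal values, m is 0 with none removed, about 0.098 with 1 removed, 0.182 with 2 and 0.333 with 4. False-positive rates come from simulation (40,000 trials per row).

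| Removed, moxibustion / control | ρ | Bias (SD) | False positives favouring moxibustion |
|---|---|---|---|
| 4 / 0 | 0.5 | 0.5 × 0.333 = 0.17 | about 7% |
| 4 / 0 | 0.3 | 0.3 × 0.333 = 0.10 | about 5% |
| 4 / 0 | 0.2 | 0.2 × 0.333 = 0.07 | about 4% |
| 4 / 1 | 0.5 | 0.5 × (0.333 − 0.098) = 0.12 | about 6% |
| 4 / 2 | 0.5 | 0.5 × (0.333 − 0.182) = 0.08 | about 4.5% |
| 4 / 4 | 0.5 | 0 | close to nominal |
| 4 / 0 | −0.5 | −0.17 (against moxibustion) | below nominal |

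A different model gives the same order of size. Suppose a share f of 10% to 30% are poor compliers whose outcome is d = 0.5 to 1 SD worse. Removing them from moxibustion only gives a bias of f × d, from 0.1 × 0.5 = 0.05 to 0.3 × 1 = 0.30 SD, with two-sided type I error of 5.5% to 10.3%. With half as many also removed from control, the bias is 0.03 to 0.17 SD and the error 4.9% to 6.6%.

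For scale, 20 per arm detects (1.960 + 0.842) × √(2/20) = 0.89 SD with 80% power.

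**The case against.** The strongest reply is that the text does not mandate any of this harm. Termination is optional, participants are encouraged to complete all evaluations, and discharge data are required and may be taken at the scheduled time. No section says that terminated participants are dropped or that early values count as week 8. The analysis population and the handling of early values are commonly left to an analysis plan, which may exist and is not shown. The illustration deletes patients whose data section 2.5 asks for, and its removal rate, correlation, sign and one-sidedness are all assumed.

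Most of this stands, and it rules out three stronger readings that a reader might infer:
- **That the rule can remove only moxibustion patients.** Criterion 4 concerns compliance with the whole protocol, and waiting-group participants can breach it by missing assessments.
- **That terminated participants contribute only an exit measurement.** The scheduled discharge is expressly an option.
- **That unmasked staff decide the removals and the randomised comparison is thereby broken.** The text does not say who decides; the Conclusion says only that the treating physician cannot be blinded and the outcome assessor is. Bias needs a further step that the protocol permits but does not state.

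The reply does not remove the core point. Whether outcomes are collected after poor compliance is a matter of conduct, and on that point section 2.5 allows either course.

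**Conclusion.** The point holds as a conditional one. The protocol permits compliance-related termination from the study, probably mainly in the moxibustion arm, and does not fix when the final measurement is taken. This can bias the comparison if scheduled outcomes are then missed or an early exit value is used as the week 8 value.

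With 4 of 20 removed from moxibustion only and a correlation of 0.2 to 0.5, the bias is about 0.07 to 0.17 SD in favour of moxibustion, and false positives in that direction are about 4% to 7% against 2.5%. This is modest beside the 0.89 SD that the trial could detect. It falls as control losses rise, is about zero when losses are equal, and changes sign if those who improve are the ones who stop attending. None of these inputs is in the document, so neither size nor direction should be read as a prediction. The case for acting is that the correction is cheap and must be in place before data are lost.

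**What to change.** In section 2.5:
1. Separate stopping sessions from leaving the study. State that poor compliance with sessions does not end follow-up.
2. State that every randomised participant is assessed at the planned visit 12, 24 and 25 time points (weeks 4, 8 and 12) unless consent to follow-up is withdrawn.
3. Replace the choice between exit and scheduled discharge with assessment at the scheduled time. Any additional exit measurement is recorded at its actual time and is not used as the week 8 value.
4. State that participants are analysed in their allocated arm, if the analysis plan does not already say so.

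These changes concern follow-up and analysis only. When treatment stops remains a clinical decision and is not altered.

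Cost: some wording, and up to three assessments for each affected participant. The estimate will include non-adherent patients and may be slightly smaller.

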### Recruitment and randomization

2.6

Who signed the inform consents participants will be subjected to the measurement of vital signs (eg, blood pressure, pulse rate, and body temperature), demographic information survey, medical history (eg, past, present, and family), and physical examination. Eligible participants who meet the inclusion and exclusion criteria will receive a schedule of clinical trials.

The randomization at a 1:1 ratio into the 2 study arms will be performed via a computer-generated randomization list (prepared by SAS Visual Data science Decisioning, SAS Institute Inc., Cary, NC), which will be kept at the TCM Skill Training Center, Xiamen University Malaysia. Randomization will be stratified by the TCM Skill Training Centre. This computer-generated randomization list show only one result at a time and is unavailable to the enrolling study clinical researcher.

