**Methods::**

This study will be a pilot, interventional, randomized, 2-armed, parallel, singled-masked, controlled trial. A total of 40 diabetes mellitus patients with peripheral neuropathy will be recruited and assigned randomly into 2 groups (moxibustion group and waiting group) at a 1:1 ratio. This trial consists of an 8-week intervention period and a 4-week follow-up period. During the intervention period, the moxibustion group will take 3 moxibustion sessions per week, whereas no intervention will be done on the waiting group to act as the control group. The outcome will be assessed by an outcome assessor who is unaware of the group assignment. The primary outcome will be pain assessment measured with algometry, Leeds Assessment of Neuropathic Symptoms and Signs pain scale, visual analogue scale, and neuropathy pain scale. The secondary outcome will be an evaluation of functional performance capacity with 6 minutes walking test, evaluation of the Foot and Ankle Ability Measure, and serum HbA1c and albumin levels.

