### Study design and setting

2.2

This study is designed as a pilot, interventional, randomized, 2-armed, parallel, singled-masked, controlled trial. This study will be conducted at TCM Skill Training Centre, Xiamen University Malaysia from November 2021 to December 2023. A total of 40 diabetes mellitus patients with peripheral neuropathy will be recruited to participate in this trial and will be assigned randomly into 2 groups (moxibustion group and waiting group) at 1:1 ratio. The outcome assessor in this study will be unaware of the group assignments. This trial consists of 8-week intervention period and 4-week follow-up period. The study design is illustrated in a flow chart in Figure 1. Present clinical trial study has not completed participant recruitment at the time of submission.

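### Randomisation is said to be stratified by the trial's only centre, so the factor has one level and, with about 20 per arm, only chance balances baseline pain

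*Protocol article*

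**What the plan says.** Section 2.6 (Recruitment and randomization) describes the method as follows: "The randomization at a 1:1 ratio into the 2 study arms will be performed via a computer-generated randomization list". It then names one stratification factor: "Randomization will be stratified by the TCM Skill Training Centre". No second factor appears.

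Section 2.2 (Study design and setting) gives the location: "This study will be conducted at TCM Skill Training Centre, Xiamen University Malaysia from November 2021 to December 2023". Section 2.8.1 (Intervention group) confirms it for treatment: "patients of intervention group will receive moxibustion treatment provided by registered physician at TCM Skill Training Centre, Xiamen University Malaysia".

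On size, section 2.2 states that "A total of 40 diabetes mellitus patients with peripheral neuropathy will be recruited to participate in this trial" and that they "will be assigned randomly into 2 groups (moxibustion group and waiting group) at 1:1 ratio".

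The primary outcome is pain on four instruments (section 2.9.1), all measured at visit 1 (section 2.7). The inclusion criteria (section 2.4.2) require proven neuropathy but set no pain level. The Data analysis section names a t test for matching data or a Wilcoxon test, and no baseline covariate.

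**The concern.** Stratifying by site balances the arms within each site, so it needs at least two sites. Here every participant belongs to the same one, and the stated stratification changes nothing. A reader of the protocol, or later of the results paper, would believe that the allocation had a balancing feature which it lacks.

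Precision and credibility are at stake. Baseline pain is likely to be strongly related to later pain, and eligibility does not restrict it. In a trial of 40, a visible baseline difference on a pain score is quite possible. The one analysis sentence does not say that such a difference would be taken into account.

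**Working it through.** The plan gives no figure for imbalance, power or effect size, so there is nothing to reproduce. The check has five steps.

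**1. Number of strata.** The factor is the centre (section 2.6), and there is one centre (sections 2.2 and 2.8.1). One level means one stratum, and a list drawn within that stratum is the list for the whole trial. This is unstratified randomisation.

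**2. Arm size.** 40 patients at 1:1 gives 40/2 = 20 per arm.

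**3. Chance imbalance on one baseline pain score, in SD units.**
- SE of the difference = sqrt(1/20 + 1/20) = sqrt(0.1) = 0.316 SD.
- Above 0.3 SD: 2 × [1 − Φ(0.3/0.316)] = 0.343.
- Above 0.5 SD: 2 × [1 − Φ(0.5/0.316)] = 0.114.
- 95% range: ±1.96 × 0.316 = ±0.62 SD.
- A simulation of 200,000 random 20:20 splits of normal scores gave SE 0.317 and probabilities 0.343 and 0.114.

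**4. What an imbalance does to an unadjusted comparison of final scores.** A baseline difference d shifts the final difference by about ρ × d, where ρ is the correlation between baseline and final score. The documents do not give ρ, so it is assumed over a range. For d = 0.5 SD:

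| Assumed ρ | Shift in final difference |
|---|---|
| 0.3 | 0.3 × 0.5 = 0.15 SD |
| 0.5 | 0.5 × 0.5 = 0.25 SD |
| 0.7 | 0.7 × 0.5 = 0.35 SD |

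The shift is equally likely to favour either arm, so it is extra noise and not a systematic error.

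**5. What each remedy buys.**
- *A real stratum.* For illustration, take a split at the median of baseline pain, with 10 and 10 allocated in each half and normal scores. In the same simulation the SE of the baseline difference falls from 0.317 to 0.193 SD. The chance of a difference above 0.3 SD falls from 34% to 12%, and above 0.5 SD from 11% to 1%. A split at LANSS 12 need not fall at the median and could do less.
- *Baseline adjustment.* Analysis of covariance multiplies the residual variance by 1 − ρ². Under an assumed true difference of 0.8 SD (normal approximation, two-sided 5%), power rises from 72% unadjusted to 76%, 83% and 94% for ρ = 0.3, 0.5 and 0.7, before the small loss shown next.
- *What imbalance costs once adjustment is made.* The adjusted variance is inflated by (d²/38)/0.1. For d = 0.5 this is (0.25/38)/0.1 = 6.6%, or about 3% in the SE. On average the inflation is about 1/36, or 3% in variance. Adjustment alone therefore recovers most of what stratification would offer.

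**The case against.** The strongest reply is that the empty sentence does no harm in itself. If it is deleted, the trial runs exactly as before. The 11% applies to any trial randomised 20:20 without stratification on pain, and leaving pain unstratified is a legitimate choice in a pilot. This stands: the protocol is not at fault for failing to stratify on pain. It is at fault for stating a stratification that cannot exist. If the sentence meant that the centre carries out the randomisation, it is still wrongly worded, and no factor is named at all.

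Three stronger readings are tempting, and the documents do not support them.
- A reader might infer that the comparison is biased or the test invalid. It is not. Randomisation balances the arms in expectation, and the error rate of a between-arm test already allows for chance imbalance. Section 2.6 also says that the list reveals one result at a time and is withheld from the enrolling researcher.
- A reader might infer that there is no blocking and that the arm sizes could drift apart. The article does not describe blocks, but that detail is commonly left to the full protocol. Its absence is no finding, and a figure for unequal arms would rest on assuming simple randomisation, which nothing here states. Blocks alone would not balance baseline pain in any case.
- A reader might infer a known mix of painful and painless neuropathy. Eligibility sets no pain level, but section 2.9.1 says that the NPS is for patients already diagnosed with neuropathic pain. The intended mix is unclear, and the documents give no share above LANSS 12.

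**Conclusion.** The point holds as an error of statement with a modest statistical consequence. The stratification factor has one level, and no fuller protocol or analysis plan can turn one named centre into two strata. Balance on baseline pain is left to chance, with probability about 11% of a difference above 0.5 SD on a given score and about 34% above 0.3 SD. These figures assume arms of 20 and approximately normal baseline means. They do not depend on any assumed share of patients above a pain threshold. The cost is in precision and credibility. The validity of a between-arm test is unaffected.

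**What to change.** Take one of two routes for the sentence in section 2.6.
1. Delete the stratification claim and describe the allocation as unstratified.
2. Replace the centre with a real factor already measured at visit 1, for example LANSS below 12 versus 12 or more, scored before allocation. Use concealed permuted blocks that are not so small as to be guessable. This matters in a single-centre trial with an untreated control, where those giving treatment know the allocation. Very small blocks, such as 2, would let the next allocation be worked out.

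In either case, state in the Data analysis section that the between-arm comparison of each pain outcome is adjusted for its own visit 1 value, and for the stratum if one is used.

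The cost is small. Baseline adjustment needs no new data. The second route needs a regenerated list for the patients still to be enrolled; section 2.2 says that recruitment was incomplete at submission, and patients already allocated would stay as they are. It also needs the order of visit 1 to be fixed: the checks before randomisation listed in section 2.6 do not include LANSS, and section 2.7 puts it at the same visit as the first treatment session.
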